### Primary endpoints

Contrasts between study arms: we will assess the non-inferiority of the experimental arm versus the standard arm in detecting ISUP $\geq 2$  cancers ( $\delta = 0.04$  or  $\exp(-\delta) = 0.78$ , as appropriate). The  $\alpha$  level is set to 0.025. Two-sided 95% confidence intervals will be reported.

Contrasts within study arms: we will assess the non-inferiority of the Stockholm3 test versus PSA in detecting ISUP $\geq 2$  cancers ( $\exp(-\delta) = 0.78$ ) and the superiority of PSA versus the Stockholm3 test in detecting ISUP1 cancers (i.e. a lower proportion of ISUP1 cancer detected according to the Stockholm3 test) ( $\exp(-\theta) = 1$ ). The  $\alpha$  level is set to 0.025 for both tests. Two-sided 95% confidence intervals will be reported.

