### Key secondary aims

1. To test whether targeted prostate and systematic biopsies performed in MRI positive men will lead to: non-inferior sensitivity for detecting clinically significant cancer (ISUP grade group  $\geq 2$ ); reduced number of performed biopsy procedures; and lower proportion of men with elevated risk who experience severe post-biopsy infections compared to systematic biopsies for men with elevated risk (defined as being positive on PSA and/or Stockholm3) of prostate cancer in prostate cancer screening.
2. To test whether targeted prostate biopsies performed in MRI positive men will lead to: non-inferior sensitivity for detecting clinically significant cancer (ISUP grade  $\geq 2$ ); reduced number of performed biopsy procedures; and lower proportion of men with elevated risk who experience severe post-biopsy infections compared to systematic biopsies for men with elevated risk (defined as being positive on PSA and/or Stockholm3) of prostate cancer in prostate cancer screening.
3. To test whether a diagnostic chain consisting of Stockholm3 followed by MRI and targeted+systematic biopsies versus a diagnostic chain based on PSA  $\geq 3$  ng/ml followed by MRI and targeted+systematic biopsies will lead to: non-inferior sensitivity for detecting clinically significant cancer (ISUP grade group  $\geq 2$ ); an inferior sensitivity for ISUP1 cancers (i.e. reduced overdiagnosis); and a reduction in the number of MRI examinations and performed biopsies.
4. To test whether a diagnostic pathway using the Stockholm3 test to select men for further workup using MRI followed by ONLY targeted biopsies (S3M+MRI+TBx) has non-inferior sensitivity for detecting clinically significant cancer (ISUP grade  $\geq 2$ ) and reduces the number of performed biopsy procedures compared with a diagnostic pathway using systematic biopsies in men with PSA  $\geq 3$  ng/mL (PSA+SBx).

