#### *Non-inferiority and superiority tests*

The null and the alternative hypothesis for a non-inferiority test for the  $\Delta DP$  are:

$$\begin{aligned} H_0: \Delta DP &\leq -\delta \\ H_a: \Delta DP &> -\delta \end{aligned}$$

where  $\delta > 0$  is the non-inferiority margin. This means that non-inferiority for a specific endpoint will be claimed if the lower boundary of the two-sided  $(2\alpha \times 100)\%$  confidence interval for the  $\Delta DP$  does not cover  $-\delta$ .

The null and the alternative hypothesis for a superiority test for the  $\Delta DP$  are:

$$\begin{aligned} H_0: \Delta DP &\leq \theta \\ H_a: \Delta DP &> \theta \end{aligned}$$

where  $\theta \geq 0$  is the superiority margin. This means that superiority for a specific endpoint will be claimed if the lower boundary of the two-sided  $(2\alpha \times 100)\%$  confidence interval for the  $\Delta DP$  does not cover  $\theta$ .

For comparisons on a relative scale (rTPF), the null and the alternative hypothesis for non-inferiority and superiority tests are

$$H_0: rDP \leq \exp(-\delta)$$

$$H_a: rDP > \exp(-\delta)$$

and

$$\begin{aligned} H_0: rDP &\leq \exp(\theta) \\ H_a: rDP &> \exp(\theta) \end{aligned}$$

respectively, with non-inferiority and superiority margins equal to  $\delta > 0$  and  $\theta \geq 0$ .

One-sided p-values will be calculated based on the test considered (non-inferiority or superiority).

Switching from non-inferiority to superiority: if the two-sided  $(2(1 - \alpha) \times 100)\%$  confidence interval for  $\Delta DP$  (rTPF) not only lies entirely above the non-inferiority margin, but also above the superiority margin, superiority will be claimed at the same alpha-level set for the non-inferiority test. In this case, we will also calculate the p-value associated with a test for superiority.

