#### *Updated sample size calculations (performed during Spring and Summer 2019)*

We revised the sample size calculations above in order to have sufficient statistical power to answer comparisons of Stockholm3 vs. PSA within the experimental arm.

The updated, final sample size is the result of a balance between time and financial constraints on one hand and the need to maximise the power for contrasting Strategies 6 vs. 3 on the other hand. In fact, different assumptions about the joint probability of  $ISUP \geq 2$  and screening positive on the PSA test [ $Pr(ISUP \geq 2, PSA \geq 3 \text{ ng/ml})$ ] and about the TPF of the PSA test [ $Pr(PSA \geq 3 \text{ ng/ml} | ISUP \geq 2)$ ] lead to different required sample sizes.

Based on the sample size calculation, we decided to increase the number of men invited into the study to ~50000. Based on an updated estimate of the expected participation rate (25%), this will lead to ~12500 men included in the study and to ~2100 randomised men based on PSA or Stockholm3 (assuming ~16.5% of the enrolled men will test positive on either screening test; 13% passed on PSA alone, leading to ~1600 randomized men with  $PSA \geq 3 \text{ ng/ml}$ ), ~1700 of whom will complete the diagnostic chain, assuming a 20% drop-out rate.

The updated sample size will give:

1. 50–90% power for the contrast S3M+TBx+SBx versus PSA+TBx+SBx. This is based on the following assumptions: 0.015–0.03 probability of detecting  $ISUP \geq 2$  and screening positive on the PSA test (Grönberg et al. 2015), 0.57–0.63 TPF for the PSA test (Thompson et al. 2005),  $rTPF$  (Stockholm3  $\geq 11\%$  vs  $PSA \geq 3$ ) equal to 1 (Grönberg et al. 2015), and a conservative DDR estimate (Alonzo, Pepe, and Moskowitz 2002). The non-inferiority margin was set to  $\delta = -\log(0.78)$  and alpha to 0.025.

Note: the contrast S3M+TBx+SBx versus PSA+TBx+SBx is nested within the experimental study arm, where about 7500 men will be included (due to the 2:3 randomisation). We further assumed a 20% drop-out rate, leading to 6000 men available for the analyses.

| DR_psa | TPR_psa | power |
|--------|---------|-------|
| 0.015  | 0.57    | 0.48  |
| 0.020  | 0.57    | 0.60  |
| 0.025  | 0.57    | 0.70  |
| 0.030  | 0.57    | 0.77  |
| 0.015  | 0.59    | 0.52  |
| 0.020  | 0.59    | 0.64  |
| 0.025  | 0.59    | 0.73  |
| 0.030  | 0.59    | 0.81  |

|       |      |      |
|-------|------|------|
| 0.015 | 0.61 | 0.55 |

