| 0.020 | 0.61 | 0.67 |
| 0.025 | 0.61 | 0.77 |
| 0.030 | 0.61 | 0.84 |
| 0.015 | 0.63 | 0.59 |
| 0.020 | 0.63 | 0.71 |
| 0.025 | 0.63 | 0.80 |
| 0.030 | 0.63 | 0.87 |

2. More than 90% power for the contrast PSA+MRI+TBx+SBx vs PSA+SBx (rDP = 1.3, noninferiority margin for  $\Delta DP \delta = 0.04$ ,  $\alpha = 0.025$ ).

Thus, contrast 1 drives the required samples size of the study. We therefore powered the study (with respect to sample size for sending out invitations and enrolling participants) to have sufficient statistical power to answer comparisons of Stockholm3 vs. PSA within the experimental arm.

Note: no correction for multiple comparisons was made. This means that each of the three tests (with respect to the ISUP 2, ISUP 1, and biopsy endpoints) has an approximate type I error rate of 2.5% if the corresponding null hypothesis is true. If all three null hypotheses are true and we assume the tests to be independent, the overall type I error rate is approximately 7%. In reality however, these hypotheses are strongly correlated. Thus, the overall type I error rate is bounded below by 2.5% and above by 7%.

R code for the power calculations is available at:

<https://gist.github.com/anddis/fc1a265d102b509b0eacd59ab065661a>

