### Additional analyses

Due to updates in the Stockholm3 assay system to reduce measurement errors in the biomarkers included in the Stockholm3 risk prediction model, Stockholm3  $\geq 11\%$  as a selection criterion for randomization may be more sensitive than PSA  $\geq 3$  (i.e. more men with clinically significant prostate cancer will be randomized based on the criterion Stockholm3  $\geq 11\%$  compared with PSA  $\geq 3$ ). If this turns out to be true, we will perform analyses where we “count backwards” (increase the S3M cutoff) and compare biopsy rates at identical sensitivity for clinically significant prostate cancer when comparing diagnostic strategies involving S3M compared with PSA  $\geq 3$  (as described in Grönberg et al.).

We will artificially randomise (2:3) those men who screened negative on both screening tests. By doing this, the totals [d]+[h] and [d']+[h'] will become known, which in turn will allow the estimation of quantities like  $\Pr(\text{ISUP} \geq 2, \text{Stockholm3} \geq 11\% \mid \text{Standard arm})$  (i.e., the probability of ISUP  $\geq 2$  and Stockholm3  $\geq 11\%$  in enrolled men randomised to the standard arm). Contrasts between the two study arms with respect to these quantities will be

---

 Where applicable.

performed using the same methodology described in the section “Contrasts between study arms (unpaired design)”.

We may in additional analyses use regression models to model the DP, TPF, and FPF given covariates. We will employ standard generalised linear models or marginal models (Pepe and Alonzo 2001), as appropriate.

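### For Strategy 6 vs 3, no planned test asks whether the fall in ISUP 1 cancers and biopsies exceeds the loss of ISUP ≥2 cancers, and the equal-sensitivity analysis runs in one direction only

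*Combined protocol and SAP*

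**What the plan says.** SAP, Primary endpoints, sets two within-arm tests. One is non-inferiority of Stockholm3 to PSA for ISUP ≥2 at a ratio of 0.78. The other is "the superiority of PSA versus the Stockholm3 test in detecting ISUP1 cancers (i.e. a lower proportion of ISUP1 cancer detected according to the Stockholm3 test", with a null ratio of 1. The alpha "level is set to 0.025 for both tests". Key secondary endpoints repeats the ISUP 1 test.

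SAP, Key secondary aims (aim 3), adds "a reduction in the number of MRI examinations and performed biopsies" and gives no minimum size. The multiplicity note under Updated sample size calculations refers to "each of the three tests (with respect to the ISUP 2, ISUP 1, and biopsy endpoints", so a biopsy test is intended, but no null is written for it. I take a ratio of 1.

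SAP, Contrasts within study arm, gives the interval for the relative true positive fraction (rTPF) and says the relative false positive fraction (rFPF) is handled in the same way. No test compares the two.

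SAP, Additional analyses, plans to raise the Stockholm3 cut-off and "compare biopsy rates at identical sensitivity for clinically significant prostate cancer", but only if Stockholm3 ≥11% proves more sensitive than PSA ≥3. Publication 2 makes the same condition for contrast 6 vs 1. Nothing equivalent is planned for the opposite case.

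**The concern.** Publication 2 is meant to show whether Stockholm3 improves the choice of men for MRI. Any rule that works up fewer men lowers MRIs, biopsies and ISUP 1 detections, whether or not it discriminates better. If ISUP ≥2 detection may fall to a ratio of 0.78 while the other counts need only fall below 1, a rule that loses all of them in equal proportion can meet each test. The result could then be reported as non-inferior sensitivity with less overdiagnosis when the selection is no better.

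Comparison at equal sensitivity separates the two explanations, and the SAP plans it in one direction only. If Stockholm3 detects slightly more ISUP ≥2 cancers by chance, the excess is converted into saved biopsies. If it detects slightly fewer by chance, no adjustment is made.

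**Working it through.** **Inputs**
- Margin 0.78, null 1 for ISUP 1, two-sided 95% intervals: SAP, Primary endpoints.
- "We further assumed a 20% drop-out rate, leading to 6000 men available for the analyses", with 0.015–0.03 of them PSA-positive with ISUP ≥2: 90–180 cancers (SAP, Updated sample size calculations).
- Biopsied PSA-positive men in the experimental arm: 1600 × 0.6 × 0.8 = 768 completing; with 55% MRI-negative (Protocol Addendum), 768 × 0.45 ≈ 346.
- Discordance, meaning Stockholm3-only men as a share of PSA-positive men: (16.5 − 13)/13 = 27%. From the rounded counts, (2100 − 1600)/1600 = 31%.
- ISUP 1 count: not in the documents. Assumed half the ISUP ≥2 count (45–90), with 30 as a low case.

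**The plan's own figure.** SE² = (2·TPF − 2·TPPF)/(TPF²·n), where n = 6000·DR/TPF and minimal overlap gives TPPF = 2·TPF − 1. Power = Φ(0.2485/SE − 1.96), since −log 0.78 = 0.2485.
- DR 0.015, TPF 0.57: n = 157.9, SE = 0.1295, power 0.484 (SAP 0.48).
- DR 0.030, TPF 0.63: n = 285.7, SE = 0.0808, power 0.868 (SAP 0.87).

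All 16 cells agree within rounding.

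**A rule with no added discrimination.** Set every true ratio to 0.90. The SAP's interval is exp(log ratio ± 1.96·√[(b+c)/((a+b)(a+c))]), where b counts Stockholm3-only and c PSA-only men. At expected counts with 180 ISUP ≥2 cancers:
- b = 0 (pure random omission): SE = √(18/(162 × 180)) = 0.025; interval 0.86–0.95.
- b = 27%, c = 37%: SE = √(115.2/(162 × 180)) = 0.063; interval 0.80–1.02.

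Simulated pass rates follow (200,000 replicates; c binomial, b Poisson, cancers counted among the biopsied men). The three figures are for 90, 120 and 180 ISUP ≥2 cancers.

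| Discordance | ISUP ≥2 | ISUP 1 | Biopsies | All three |
|---|---|---|---|---|
| 0 | 94, 97, 99.8% | 67, 86, 98% | 100% | 63, 84, 98% |
| 5% | 79, 88, 97% | 30, 40, 59% | 99% | 24, 35, 57% |
| 27% | 36, 46, 62% | 10, 14, 20% | 66% | 3, 5, 10% |

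Multiplying the three pass rates as if the tests were independent gives 23–57% in the second row and 2.5–8% in the third. At 31% discordance all three pass in 2–8%. With only 30 ISUP 1 cancers the last column becomes 33–35%, 17–20% and 2–4%.

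With b = 0 Stockholm3 can never be the more sensitive test, so the equal-sensitivity analysis is never triggered.

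**The case against.** A reader might infer that simply leaving out a random tenth of PSA-positive men passes the whole set of tests. The documents do not support that as a realistic case. It needs Stockholm3 to add no PSA-negative men, whereas the SAP plans 16.5% positive on either test against 13% on PSA. The 63–98% figures belong to that extreme alone. The power calculation assumes still more disagreement among cancers: at TPF 0.63 the minimal overlap is 0.26, so (0.63 − 0.26)/0.63 = 59% of Stockholm3 detections are in PSA-negative men.

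A reader might also infer a joint success rule. There is none: the SAP lists separate tests, each at 2.5%. Nor is equal-sensitivity analysis the only thing that would reveal a non-discriminating rule. The rFPF will be estimated, and ratios near 0.90 for every endpoint would be visible to an attentive reader.

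The one-way direction has a stated reason, since assay updates may have made Stockholm3 ≥11% the more sensitive test. The analysis is also additional, and it leaves the prespecified tests unchanged. PSA ≥3 is the comparator because the mortality evidence rests on PSA-based screening, so a raised PSA cut-off cannot replace it.

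All of this stands, and it limits the size of the point. It does not supply the missing comparison of rFPF with rTPF, and it does not justify reporting the matched analysis only when it favours Stockholm3.

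**Conclusion.** The point holds as a gap in interpretation, not as an error in any one test. When every true ratio is 0.90, rejecting both the 0.78 null and the null of 1 is correct. What does not follow is that Stockholm3 selects better.

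At the discordance implied by the planning figures, the three results coincide without added discrimination in about 3–8% of trials, or 10% at most when the tests' correlation is kept. At 5% discordance the figure is about 23–57%. These figures rest on equal discordance in every cell, an assumed ISUP 1 count, and a null of 1 for biopsies inferred from the aims and the multiplicity note. The documents do not give discordance within the cancer cells.

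The one-way trigger is a matter of wording and needs no simulation to establish. Its direction of bias is clear. Its size depends on the joint distribution of the two tests, which the documents do not give.

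**What to change.** 1. Keep PSA ≥3 against Stockholm3 ≥11% as the main result. Make the additional matched-sensitivity analysis two-way: report it whichever test detects more ISUP ≥2 cancers, raise the analysis cut-off of the more sensitive test until detections match, and compare MRIs, biopsies and ISUP 1 there. All men above a higher cut-off on either test were already referred for work-up.

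2. Prespecify D = log(ratio of biopsies without ISUP ≥2) − log(ISUP ≥2 ratio). In the SAP's cell notation, restricted to biopsied men, D = log[(e+f)/(e+g)] − log[(a+b)/(a+c)]. Its variance is (f+g)/((e+f)(e+g)) + (b+c)/((a+b)(a+c)); the terms add because the two groups of men are disjoint. Describe the result as better selection only if the upper 95% limit of exp(D) is below 1. Report the ISUP 1 version alongside.

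In the simulations above, this contrast fires in about 2–5% of trials when there is no added discrimination. The cost is SAP wording, a small amount of code and a harder claim to support.

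With equal sensitivity, 32% fewer biopsies and 17% fewer low-grade cancers (Protocol 8.2), the contrast was met in essentially every simulated trial with 90–120 ISUP ≥2 cancers at 5–27% discordance, so it cost no power there. Those percentages come from systematic biopsy without MRI. They cannot all hold with 180 ISUP ≥2 and 90 ISUP 1 cancers among 346 biopsies: 180 + 0.83 × 90 = 255 exceeds 0.68 × 346 = 235. The power cost after MRI selection is therefore less certain.

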### Key secondary endpoints

Contrasts between study arms: we will assess the superiority of the standard arm versus the experimental arm in detecting ISUP1 cancers (i.e. a lower proportion of ISUP1 cancer detected in the experimental arm) ( $\theta = 0$  or  $\exp(-\theta) = 1$ , as appropriate). The  $\alpha$  level is set to 0.025. Two-sided 95% confidence intervals will be reported.

Contrasts within study arms: we will assess the superiority of PSA versus the Stockholm3 test in detecting ISUP1 cancers (i.e. a lower proportion of ISUP1 cancer detected according to the Stockholm3 test) ( $\exp(-\theta) = 1$ ). The  $\alpha$  level is set to 0.025. Two-sided 95% confidence intervals will be reported.

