### **8.3. *Traditional evaluation of men with increased risk of prostate cancer***

Men at increased risk of prostate cancer - commonly estimated using PSA and palpatory findings - are traditionally assessed using systematic prostate biopsies. The procedure is performed under local anesthesia using antibiotic prophylaxis and includes 10-12 cores taken from predefined areas of the peripheral zone of the gland as visualized by endorectal ultrasound. While the biopsies systematically covers the prostatic gland rather than targeting a lesion, and non-lethal tumors are common, the risk of over-diagnosis (i.e. detection of non-significant tumors) is high. The risk of non-representative biopsy findings result in underestimation of tumor grade compared with subsequent prostatectomy in up to 40% of men undergoing surgery. The risk of severe post-biopsy infection has increased to 1-2% with increasing frequency of antibiotic resistance, further illustrating the need both to increase precision and decrease the number of performed biopsies.

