### **8.5. Targeted prostate biopsies guided by fusion technology**

Targeted biopsies of the prostate consist of imaging (MRI) detecting significant tumors and a biopsy procedure where biopsies are targeted to the tumor using various devices for guidance. While traditional endorectal ultrasound poorly identifies tumors, direction of biopsy needles can be performed in various ways. Cognitive or soft fusion is based on skilled urologists/radiologists interpreting the MRI images and directing needles solely based on the ultrasound images. The disadvantages of cognitive fusion lie in the potential for human error when attempting to mentally fuse the MRI with TRUS while aiming for cancers that are often <1 cm in diameter and the inability to track the location of each biopsy site. Hard fusion enables proper fusion of MRI information on the ultrasound image, possibly increasing precision.

Despite methodological flaws, a number of studies have investigated the value of fusion biopsies, primarily using non-randomized designs and non-screening populations (see **Error! Reference source not found.**). In 2018, Kasivisvanathan et al provided high quality evidence for men referred for prostate biopsy and showed that MRI/target biopsies are non-inferior for detection of significant cancer and decreases the number of in-significant cancers and number of biopsies as compared with systematic biopsies.

The proportion of men upgraded when comparing specimen from targeted biopsies and subsequent prostatectomy have been shown to be very low (<5%) when using targeted biopsies, increasing the proportion of men where treatment decisions are based on valid risk estimations.

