| 20200115 | Definition, intervention | Complete pathological report is defined as containing cancer/benign AND Global Gleason. For men in the experimental arm, this should hold for both pathological reports (TBx/SBx). For men with a “negative MRI” but STHLM3 $>25\%$ this should hold for SBx pathological report.                                     | 13.4  |
| 20200115 | Definition, intervention | Global Gleason Score is defined as the highest of Systematic and Targeted Bx global scores                                                                                                                                                                                                                            | 13.4  |
| 20200115 | Definition, intervention | Complete MRI is defined as existing MRI report including PIRADS score.                                                                                                                                                                                                                                                       | 13.4  |

|            |                              |                                                                                            |      |
|------------|------------------------------|--------------------------------------------------------------------------------------------|------|
|            |                              | Complete MRI is mandatory for inclusion of experimental arm men in the PP.                 |      |
| 20200115   | Definition, Study population | Study population is defined as participating men. See further in Statistical Analysis Plan | 13.4 |
| 2020-01-29 | Definition, Study population | Participating men are defined as men with registered consent and blood sample.             | 13.4 |
|            |                              |                                                                                            |      |

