## Hypotheses

### Overarching primary hypothesis

The overarching primary hypothesis of the STHLM3MRI trial is that a diagnostic pathway using the Stockholm3 test to select men for further workup using MRI followed by targeted biopsies and systematic biopsies in MRI positive men (S3M+MRI+TBx+SBx; Strategy 6) has non-inferior sensitivity for detecting clinically significant cancer (ISUP grade  $\geq 2$ ) and shows superior specificity (reduction in number of performed biopsy procedures and detected ISUP 1 tumours) compared with the diagnostic pathway using systematic biopsies in men with PSA  $\geq 3$  ng/mL (PSA+SBx; Strategy 1).

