#### *Interpretation as relative sensitivity*

It should be noted that rDPs can (under the assumption of no false positive biopsies, see SAP Appendix 1) be interpreted as relative true positive fractions (rTPF) (ie, relative sensitivities).

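### The between-arm ISUP 1 test is valid for its own null, but a lower ISUP 1 proportion mixes low-grade diagnoses avoided with men regraded to ISUP ≥2, and the plan reads all of it as specificity.

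*Combined protocol and SAP*

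**What the plan says.** The SAP section on key secondary endpoints tests, with zero margin, whether the standard arm detects more ISUP 1 cancer ("i.e. a lower proportion of ISUP1 cancer detected in the experimental arm"). The alpha "level is set to 0.025. Two-sided 95% confidence intervals will be reported", and p-values are one-sided. The study-variable table defines the endpoint as ISUP exactly 1.

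The overarching primary hypothesis explains superior specificity as a "reduction in number of performed biopsy procedures and detected ISUP 1 tumours". The SAP text on Publication 2 goes further: it labels ISUP 1 itself as the specificity measure and lists biopsies and MRI scans separately.

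The protocol addendum (section 19) says that the Global Gleason Score "is defined as the highest of Systematic and Targeted Bx global scores". Standard-arm men have systematic cores only. Protocol section 8.3 reports that systematic biopsy leads to "underestimation of tumor grade compared with subsequent prostatectomy in up to 40% of men undergoing surgery". Section 8.5 puts upgrading after targeted biopsy below 5%, and section 16 repeats that upgrading is less of a problem in targeted cohorts.

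The SAP allows the ratio of detection probabilities (rDP) to be read as relative sensitivity "under the assumption of no false positive biopsies". Appendix 1 sets this out for any given ISUP grade and extends it to the remaining between-arm contrasts. ISUP ≥1 appears among the other secondary endpoints, but the SAP states no between-arm test for it and gives it no role in the specificity claim.

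**The concern.** With a highest-of-two grading rule, adding targeted cores can only raise a diagnosed man's grade. Consider a man with ISUP ≥2 disease whose systematic cores show ISUP 1. He counts as ISUP 1 in the standard arm. In the experimental arm, if the targeted cores hit the lesion, he counts as ISUP ≥2. He is biopsied and diagnosed either way. The ISUP 1 count falls and the ISUP ≥2 count rises, so the same shift supports both halves of the pathway's case.

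What is at stake is how the ISUP 1 part of the overarching hypothesis (6 vs 1) and the ISUP 1 results for 3 vs 1 and 9 vs 7 are read. A reader told that specificity improved will take the whole reduction as men spared a low-grade diagnosis. The planned test cannot say how much of it is that.

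**Working it through.** **What the difference contains.** Comparing the arms in expectation:

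- Fall in ISUP 1 = low-grade diagnoses avoided − ISUP 1 newly found by targeted cores + men regraded from ISUP 1 to ISUP ≥2.
- Fall in ISUP ≥1 = all diagnoses avoided − all cancers newly found. Regrading cancels.

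**Inputs.**

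- ISUP ≥2 in the standard arm: 18% of men with PSA ≥3 (SAP, original sample size assumptions).
- ISUP ≥2 ratio: 1.25 (original calculation) and 1.3 (updated calculation, 3 vs 1). The value 1.1 is added as a milder case.
- Men: about 1600 randomised with PSA ≥3 and 20% drop-out give 1280; allocation 2:3 gives 512 and 768.
- ISUP 1 in the standard arm: not given for this trial. Assumed 12–18%. The upper end follows from protocol section 8.2, where about half of cancers found by systematic biopsy are low-risk.

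**The plan's own figure first.** The SAP states more than 90% power for 3 vs 1 on ISUP ≥2 (ratio 1.3, margin 0.04, alpha 0.025). With 18% against 1.3 × 18% = 23.4%:

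- SE = √(0.18×0.82/512 + 0.234×0.766/768) = 0.0228
- Power = Φ((0.054 + 0.04)/0.0228 − 1.96) = 98.4%, in agreement.

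**Regrading only.** Let total cancer be equal in both arms, with the whole ISUP ≥2 gain taken from ISUP 1. The shift is d = 0.18 × (ratio − 1), that is 0.018, 0.045 or 0.054. With q the standard-arm ISUP 1 rate, the SAP's Wald test rejects with probability

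Φ(d/SE − 1.96), SE = √(q(1−q)/512 + (q−d)(1−q+d)/768).

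Example, q = 0.18 and ratio 1.3: d = 0.054, SE = √(0.18×0.82/512 + 0.126×0.874/768) = 0.0208, and Φ(2.60 − 1.96) = 74%.

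Each cell gives the ISUP 1 ratio, then the rejection probability:

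| Standard-arm ISUP 1 | ISUP ≥2 ratio 1.1 | 1.25 | 1.3 |
|---|---|---|---|
| 12% | 0.85; 17% | 0.625; 74% | 0.55; 89% |
| 15% | 0.88; 14.5% | 0.70; 65% | 0.64; 81% |
| 18% | 0.90; 13% | 0.75; 57% | 0.70; 74% |

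Simulation (200,000 trials) agreed to within about one percentage point. At q = 18% and ratio 1.3, 73% of simulated trials declared both ISUP ≥2 non-inferiority and ISUP 1 superiority. A test that ISUP ≥1 is lower in the experimental arm rejected in 2.5%, its nominal level.

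**Appendix 1.** The step from rDP to relative sensitivity needs a zero false-positive fraction for the grade in question. For ISUP 1, a man with true ISUP ≥2 graded 1 on biopsy is a false positive. Protocol sections 8.3 and 16 imply that this happens, and more often with systematic cores alone. The assumption therefore cannot hold for ISUP 1. It remains arguable for ISUP ≥2.

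**Contrast 6 vs 3.** Both strategies use the same man's same combined grade, so regrading does not enter.

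**The case against.** The strongest reply is that the SAP tests what it says. Its bracketed definition of specificity names detected ISUP 1 tumours, and a man with biopsy-proven ISUP ≥2 has not received a low-grade diagnosis. Within the SAP hypotheses, reduced overdiagnosis is tied to ISUP 1 only for 6 vs 3. This stands as far as the test goes: its level is correct for its own null. It does not settle the interpretation, because the Publication 2 text equates ISUP 1 with specificity, and protocol section 8.6 expects less overdiagnosis from the whole pathway.

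A reader might infer that the type I error is inflated, or that a significant ISUP 1 result would be a grading artefact. The documents do not support either. The addendum assumes 55% MRI-negative, and these men are not biopsied unless Stockholm3 is ≥25%, so much of the fall should be genuine. If avoidance alone removed 40–55% of ISUP 1 (an assumption), the test would reject in 80–99.9% of trials with no regrading at all.

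A reader might also use the 40% in section 8.3 as the undergrading rate and conclude that regrading makes rejection nearly certain. That figure is an upper limit, covers any grade underestimation, and concerns men selected for surgery. With 5% undergrading left in the experimental arm, rates of 30% and 40% imply ISUP ≥2 ratios of 0.95/0.70 = 1.36 and 0.95/0.60 = 1.58, above the planned 1.25–1.3. At 40% with 12% ISUP 1, true ISUP ≥2 is 0.18/0.60 = 30% and true ISUP 1 is 0.12 − 0.40 × 0.30 = 0, which is not credible.

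Finally, ISUP ≥1 is already a listed endpoint and can be obtained by adding two reported ones. That makes the remedy cheap, but no text links it to the specificity claim.

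**Conclusion.** The point holds as one of interpretation. For 6 vs 1, 3 vs 1 and 9 vs 7, a lower ISUP 1 proportion combines avoided diagnoses with regrading. Reading all of it as specificity overstates the avoided part by an amount that the plan does not estimate.

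The table shows that regrading alone could matter at plausible effect sizes. It rests on an assumed ISUP 1 rate, on equal total cancer in the two arms, and on contrast 3 vs 1. The values at 1.25 and 1.3 are upper bounds, because part of the planned gain may be cancers that systematic cores miss altogether; the documents give no split. Contrasts 6 vs 1 (relative scale, different screening test) and 9 vs 7 were not computed, although the mechanism is the same. The primary non-inferiority test on ISUP ≥2 is not in question. The relative-sensitivity reading in Appendix 1 does not carry over to ISUP 1.

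**What to change.** 1. In the SAP section on relative sensitivity and in Appendix 1, limit the reading of rDP as relative sensitivity to ISUP ≥2.
2. For each between-arm contrast, report the ISUP ≥1 contrast with the same type of interval beside the ISUP 1 result, together with the number of experimental-arm men whose systematic report is ISUP 1 but whose combined grade is ≥2.
3. Describe the ISUP 1 result as a lower proportion graded ISUP 1, and as fewer men diagnosed only so far as ISUP ≥1 also falls.

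Two cautions apply when reading these. ISUP ≥1 can stay level if newly found cancers offset avoided ones, which is why the regraded count belongs beside it. That count is itself approximate: experimental-arm systematic cores follow the targeted cores, and additional hypothesis 6 expects them to be more sensitive than those in the standard arm. For the same reason, an analysis that returns regraded men to the ISUP 1 count may be shown as a sensitivity analysis, but should not be a condition for any claim.

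The cost is SAP wording and a few extra table rows from separate systematic and targeted reports that are already collected. The downside is that the reduction attributed to avoided low-grade diagnosis may turn out smaller.
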